### Secondary outcome measures

As this is an unpowered feasibility study, we are not hypothesising significant changes in any secondary outcomes. However, we will explore changes in outcomes before and after the intervention, comparing the treatment and control group (TAU), and we may expect some positive trends. We are also exploring the differences between online and face-to-face groups and have no current hypothesis in terms of superiority.

### Quantitative evaluation

Data collected will be entered directly into a database hosted on REDCap by a member of the study team. REDCap is an internet cloud-based system with high-security data collection and management software. Assessments will be delivered virtually or face to face, depending on participant preference. Demographics and general information will be collected including age, gender, ethnicity, use of medication (including antidepressants, anxiolytics and cholinesterase inhibitors), treatment preference, participation in other activities and presence/absence of a carer/supporter. The baseline assessment will take approximately 90 minutes for the participant with dementia and approximately 25 minutes for the carer/supporter. We will pilot the assessment battery and if it is perceived as too arduous, we will revisit the assessments. We will ensure that we offer breaks during the assessment and hold more than one assessment session if required. There were no problems encountered conducting a similar battery assessment in our initial study.^5^ The following measures, all with good to excellent psychometric properties, will be collected by a researcher (blind to group allocation), at week zero (baseline).

### Measures to be completed by the participant

MoodCornell Scale for Depression in Dementia^12^: This scale measures symptoms of depression and rates depression in five categories including mood-related signs, behavioural disturbance and ideational disturbance, using self-rated reports from the person with dementia. Good reliability and validity have been demonstrated.Rating Anxiety in Dementia^13^: This rates signs and symptoms of anxiety using interviews with people with dementia. There are 18 questions in 4 categories: worry, apprehension, vigilance, motor tension and autonomic hypersensitivity. A score of 11 or above indicates significant clinical anxiety. It has good inter-rater and test–retest reliability and is sensitive to change.Quality of lifeThe Dementia Quality of Life (DEMQOL) instrument is included because quality of life has been linked to mood in dementia. It measures five domains of quality of life; health and well-being, cognitive functioning, social relationships and self-concept. The scale uses self-rated reports of quality of life from the person with dementia. It has high internal consistency (0.87) and acceptable inter-rater reliability (intracluster correlation, ICC 0.84)^14^The EuroQol 5-Dimension 5-Level (EQ-5D-5L)^15^ is included because quality of life has been linked to mood in dementia. It measures five domains of the participant’s health-related quality of life (mobility, self-care, usual activities, pain/discomfort and anxiety/depression). The scale uses self-rated reports of quality of life from the person with dementia. It has good internal consistency and inter-rater and test–retest reliability.Two quality-of-life measures are used because EQ-5D-5L supports quality-adjusted life-years (QALYs) calculations in health economic evaluations, while DEMQOL is recommended by National Institute for Health and Care Excellence (NICE) guidelines for assessing quality of life in dementia patients.Cognitive functionThe Montreal Cognitive Assessment^16^ will enable us to explore whether mood is a predictor of cognitive change. It is a 30-point test consisting of 13 tasks covering 8 domains: visuospatial/executive functions, naming, verbal memory registration and learning, attention, abstraction, delayed verbal memory, and orientation. It has demonstrated high sensitivity and specificity.Self-compassionThe Short-Self-Compassion Scale^17^ measures self-kindness, self-judgement, common humanity, isolation, mindfulness and overidentification. It has good internal consistency (α≥0.86), factorial validity and convergent validity. It has not been specifically validated for use in dementia populations although was completed successfully in our pilot study.^5^ We will look at the validation data within our analysis.Relationship with caregiverThe Quality of Caregiver and Patient Relationship (QCPR) scale^18^ is a 14-item scale measuring relationship quality, it has displayed good psychometric properties and internal consistency, with a Cronbach’s alpha of 0.82. For those who have a caregiver, it will be rated by both the person with dementia and their caregiver enabling both perspectives to be examined.Resource useThe Client Service Receipt Inventory (CSRI)^19^ is used extensively in economic studies of dementia: it gathers data on accommodation, medication, use of public, private and voluntary sector services and inputs from carers/supporters.

### Measures to be completed by the carer/supporter (if applicable)

Relationship with caregiverAs described above, the QCPR scale^18^ will be implemented to gain the caregivers’ perspective.Caregiver burdenThe revised Zarit Burden Interview (ZBI)^20^ consists of 22 items rated on a 5-point Likert scale that ranges from 0 (never) to 4 (nearly always) with the sum of scores ranging between 0 and 88. Higher scores indicate greater burden. The ZBI is used extensively to assess caregiving burden in clinical and research settings.Quality of LifeThe EQ-5D-5L proxy will be used to calculate QALYs in line with NICE guidance.^15^ The DEMQOL-proxy will also be administered.

### Qualitative evaluation

Group facilitators will complete an attendance register and a fidelity checklist to determine if the intervention is delivered and adhered to as intended. All sessions will be audio recorded, and an independent researcher will rate fidelity with a random 10% of the recordings. We will conduct semistructured, audio recorded interviews with up to 20 participants with dementia (including up to 10 control group participants with dementia, to explore trial and intervention procedures from the perspective of those who did not participate in the intervention). We will also interview up to 15 carers/supporters (including those who did not attend the workshop to better explore barriers to attendance). We will approach and plan to interview up to 10 NHS personnel (including group facilitators and service managers) for qualitative interviews to determine feasibility of implementation.

Interview topic guides will be guided by process evaluation parameters described in recognised frameworks^21 22^ and draw on theoretical models such as normalisation process theory.^23^ Interview topic guides will be coproduced with people with dementia and their carers/supporters.

Analysis will follow Braun and Clarke’s methods of thematic analysis^24^ and will be done using NVivo. This analysis will reveal the experiences of CFT and its delivery, the barriers and facilitators to its uptake and continued use, and the perceived benefits for the person participating in CFT and how were these realised (mechanism of change). Findings will also be evaluated with a focus on implementation considerations.

### Discontinuation/withdrawal of participants

A participant may be withdrawn from the trial whenever continued participation is no longer in the participant’s best interests, but the reasons for doing so should be recorded. Reasons for discontinuing the trial may include:

Disease progression while in trial.Chronic current illness.Patients withdrawing consent or losing capacity to consent.

The decision of a participant to withdraw from treatment will be recorded in the electronic CRF and medical notes. If a participant withdraws from the intervention, they will be asked to continue to provide follow-up data. Their decisions regarding withdrawal from the intervention and withdrawal from follow-up will be recorded in their medical notes and in the trial electronic CRF, along with any reasons that they have shared.

### Recording and reporting of serious AEs and AEs

There are no known adverse effects of CFT. However, taking part may possibly cause distress/inconvenience for some participants with dementia. It is of particular importance in this trial to capture events related to the procedure (CFT). The assessment of a possible relationship of a serious AE or AE with trial procedures will be recorded and reported as part of the trial to ensure it is safe.

### Statistical analysis

A statistical analysis plan will be written, agreed and signed off before data lock is complete detailing all quantitative analysis to be conducted by NWORTH. Primary analysis will be based on the feasibility outcomes defined above. For the proposed clinical outcomes, we will conduct exploratory statistical analyses using ‘intention-to-treat’ principles. The focus of the results will be on the estimates of the treatment effects rather than statistical significance. Therefore, differences between the two comparison groups will be presented in the form of an unadjusted mean difference for continuous outcomes, and an OR for binary outcomes, with their associated 95% CIs. Given the nature of this study, no imputation methods will be used over and above any rules indicated by the measures for handling missing items. Missing data will be used to assess the suitability of the measure’s future use. Despite individual randomisation, the treatment is group based, and therefore, we will estimate the potential ICC coefficient. This, together with indications from other work, will guide the sample size of a future trial.

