## Methods and analysis

### Trial design

A single-blind feasibility RCT will compare group CFT plus treatment as usual (TAU) against TAU alone. 50 participants will be randomised to either the intervention group (CFT plus TAU) or control group (TAU). Randomisation will occur after baseline assessments are completed. Each arm will have approximately 25 participants, with up to 7 participants in each CFT group. The duration of the intervention will be 15 weeks, consisting of 12 hourly CFT therapy sessions. The 15-week block is being used to hold 12 sessions of CFT, to provide a buffer to allow for factors such as weather issues, therapist annual leave and illness, increasing the likelihood that participants will receive all 12 sessions. There will be assessments at baseline, during the 2 weeks prior to randomisation, at the end of the intervention at approximately 16 weeks and at 6 months follow-up.

To further inform our understanding of the process and feasibility of implementation, we will conduct semistructured, audiorecorded qualitative interviews with up to 20 participants with dementia, 15 carers/supporters and 10 NHS personnel (including group facilitators and service managers). These will provide insight into the feasibility of implementation and explore trial procedures from the perspectives of those who did and did not participate in the intervention or carers workshop and barriers to attendance.

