### Randomisation procedures and blinding

Participant randomisation will be undertaken remotely via a secure online system using a dynamic adaptive randomisation algorithm provided and maintained by the Clinical Trials Unit NWORTH, Bangor University^9^. Participants will have indicated whether they are able to attend face to face only, online only or can attend either session format (in addition to their preference) when they provide consent. From this, the researcher will construct ‘randomisation blocks’ based on their ability to attend either format. Once the recruiting site reaches approximately 10 recruits to a ‘randomisation block’ (ie, online or face to face), the randomisation procedure will be carried out. If there are too few participants at one site that can only attend online, then the online groups may be combined with other sites including participants from ‘Join Dementia Research’ to form one online group. The minimum number in each CFT group is 3 participants, with the maximum being 7. The results of the randomisation will be sent to the unblinded researcher and relayed to the participants, arrangements can then be made to begin the intervention or for TAU. The intervention should begin within a week of randomisation.

Due to the nature of the intervention, it is not possible to blind participants, however, researchers collecting outcome data will be blinded. As participants may accidentally unblind researchers during follow-up assessments, we will collect data on the occasions where this happens and where possible a different researcher will conduct future assessments. The trial statistician will remain blind throughout the duration of the study until the blinded analysis (detailed in the analysis plan) has been conducted and reported to the study team.

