Acceptability of the intervention to clinicians and participants will be assessed both qualitatively and quantitively. Access to technology, ability to collect outcome data and retention of the intervention will be presented descriptively from data collected in the electronic case report forms (CRFs). Access to technology and availability to travel will be assessed as part of the initial screening session by the local researcher. The research team will record ability to collect outcome data and retention of the intervention.

Preliminary efficacy of the intervention will be assessed using the quantitative measures outlined below, all with good to excellent psychometric properties, by a researcher blind to group allocation, at week zero (baseline), approximately 16 weeks and 6 months. Suitability of secondary outcome measures for a definitive RCT will be established by analysis of completion and response rates, outcome sensitivity to change as a result of the intervention and qualitative findings as to the perceived benefits and their relative importance.

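### The planned effect estimate for continuous outcomes ignores the baseline score collected before randomisation, so it is unbiased but less precise than it need be

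*Protocol article*

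**What the plan says.** The Statistical analysis section treats the clinical outcomes as exploratory and analyses them by intention to treat. It states its priority: "The focus of the results will be on the estimates of the treatment effects rather than statistical significance". From that it concludes that "differences between the two comparison groups will be presented in the form of an unadjusted mean difference for continuous outcomes". Binary outcomes get an odds ratio, and both kinds of estimate come with a 95% interval.

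The baseline scores exist and precede allocation. The text on preliminary efficacy under Primary outcome measures says that the quantitative measures are taken "by a researcher blind to group allocation, at week zero (baseline), approximately 16 weeks and 6 months". Quantitative evaluation likewise places the listed measures at week zero. Trial design adds: "Randomisation will occur after baseline assessments are completed".

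The same section gives the size: "Each arm will have approximately 25 participants, with up to 7 participants in each CFT group". Sample size expects 75% retention. No section plans a baseline-adjusted estimate.

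**The concern.** If the aim is to estimate, the more precise of two valid estimators is the natural choice. A score taken before randomisation is a valid covariate, and adjusting for it removes the part of the outcome variance that it explains. The plan gives this up by naming the unadjusted difference. Because the article specifies the estimator, this is a choice it has made and not a detail left to the statistical analysis plan.

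What is at stake is limited but real. The article intends to judge which secondary measures suit a definitive trial partly by how far they respond to the intervention. With about 20 people per arm, each scale will have its own chance imbalance at baseline, and the unadjusted difference passes a share of it into the effect estimate. One scale may then look more responsive than another for no reason other than the luck of allocation.

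**Working it through.** **Inputs from the article.** 50 randomised, about 25 per arm (Trial design); expected retention 75%, 95% CI 62% to 86% (Sample size); two-sided 95% intervals (Statistical analysis).

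**Input not in the article.** The baseline–follow-up correlation ρ. It is an assumption, so a range is shown.

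**The plan's own figure.** The article gives no precision for the treatment effects. Its retention interval does reproduce: with 37 of 50 (74%, the whole number just below 37.5), 0.74 ± 1.96 × √(0.74 × 0.26 / 50) = 0.618 to 0.862, that is 62% to 86%. Retention of 75% gives 0.75 × 25 = 18.75, so about 19 per arm and N = 38.

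**Unadjusted half-width, in SD units.** t(0.975; N−2) × √(1/n₁ + 1/n₂) = 2.028 × √(2/19) = 2.028 × 0.324 = 0.658.

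**Baseline-adjusted half-width.** Multiply by √[(1−ρ²)(N−3)/(N−4)] and replace t on 36 degrees of freedom by t on 35. The small-sample part is √(35/34) × 2.030/2.028 = 1.016. For example, at ρ = 0.5: 0.658 × √0.75 × 1.016 = 0.579.

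**Difference in change scores, for comparison.** 0.658 × √[2(1−ρ)].

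| Assumed ρ | Adjusted / unadjusted | Adjusted half-width (SD) | Change-score half-width (SD) |
|---|---|---|---|
| 0 | 1.016 | 0.668 | 0.931 |
| 0.2 | 0.995 | 0.655 | 0.832 |
| 0.3 | 0.969 | 0.637 | 0.779 |
| 0.5 | 0.880 | 0.579 | 0.658 |
| 0.6 | 0.812 | 0.535 | 0.589 |
| 0.7 | 0.725 | 0.477 | 0.510 |
| 0.8 | 0.609 | 0.401 | 0.416 |

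A simulation at 19 per arm gave ratios of 0.995, 0.968, 0.879 and 0.723 at ρ = 0.2, 0.3, 0.5 and 0.7, in agreement. Adjustment breaks even where 1−ρ² = 1/1.016², at ρ of roughly 0.2. With no loss to follow-up (25 per arm) the unadjusted half-width is 0.569 SD, against 0.498 at ρ = 0.5 and 0.411 at ρ = 0.7.

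**Chance imbalance.** The baseline difference between arms has SD √(2/19) = 0.324 outcome SDs (√(2/25) = 0.283 with 25 per arm). The probability that it exceeds 0.3 SD in either direction is 36% at 19 per arm and 29% at 25. For 0.5 SD the figures are 12% and 8%. An imbalance of size d moves the unadjusted estimate by ρ × d:

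- d = 0.3: 0.15 SD at ρ = 0.5 and 0.21 SD at ρ = 0.7
- d = 0.5: 0.25 SD at ρ = 0.5 and 0.35 SD at ρ = 0.7

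These probabilities assume that allocation does not balance on the score itself. The article names no baseline outcome score as a balancing factor.

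Clustering within the therapy groups is ignored here; it would widen both kinds of interval.

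**The case against.** The strongest reply is that little depends on this. The primary analysis is of feasibility, none of the five Stop/Review/Go criteria uses a treatment effect, and the article hypothesises no significant change in any secondary outcome. The unadjusted difference is unbiased over randomisation, and its interval already allows for chance imbalance. An interval of about ±0.6 SD says little about efficacy with or without adjustment. All of this stands, and it keeps the point modest.

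It is also fair to say that ρ is unknown and that the gain vanishes when ρ is small. Hence the range in the table.

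A further reply is that Secondary outcome measures speaks of exploring before-and-after changes by arm, so the planned difference might be one of change scores. The article does not exclude that, so a reader should not take it as settled that only follow-up means will be compared. Change scores would not answer the point, however. They gain nothing at ρ = 0.5, lose precision below it, and remain wider than the adjusted estimate at 0.7.

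Several stronger readings are tempting, but the documents do not support them:

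- **That the estimates would mostly reflect baseline imbalance.** An imbalance of 0.3 SD shifts the estimate by only 0.15 to 0.21 SD at ρ of 0.5 to 0.7, well inside the interval.
- **That these estimates will size the definitive trial.** The article names the intracluster correlation, with other work, as the guide to sample size. It does not name the treatment effect.
- **That a separate estimate per visit without imputation offends intention to treat.** That principle concerns analysis by allocated arm. People who leave the intervention are asked to continue follow-up, and the article gives its reason for not imputing: missingness is itself evidence on a measure's suitability.
- **That the randomisation blocks must be in the model.** With blocks of about 10 there would be about 50/10 = 5, costing about four degrees of freedom, and online participants may be pooled across sites, so the factor is not cleanly defined.

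**Conclusion.** The point holds as one of precision and of chance imbalance in the realised trial. It is not one of bias. The plan names an estimator that sets aside a valid covariate that it already collects, while saying that estimation is its focus.

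At about 19 per arm, adjustment would narrow the 95% interval by about 3% at ρ = 0.3, 12% at 0.5, 19% at 0.6 and a little over a quarter at 0.7. It would gain practically nothing at 0.2 or below. These sizes rest on the assumed ρ, on 75% retention split evenly between arms, and on ignoring clustering.

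The consequence is confined to exploratory outcomes and to the comparison of the scales' responsiveness, which the article weighs together with completion rates and qualitative findings. No progression decision turns on it. The change is worth making because it costs so little. The point concerns mean differences only and makes no claim about the odds ratio for binary outcomes.

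**What to change.** In the Statistical analysis section, and in the statistical analysis plan that follows from it, replace the unadjusted mean difference as the main estimate for each continuous outcome. Use a baseline-adjusted mean difference with its 95% interval, from an ANCOVA of the follow-up score on arm and the same scale's baseline score. Keep the unadjusted difference alongside.

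Report the residual SD and the baseline–follow-up correlation for each scale. Both can be computed from the data whichever effect is tabulated, and both would help if the definitive trial is to be sized for an adjusted analysis.

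The cost is one degree of freedom, a change of wording, and the need for a baseline score for each analysed participant. No new data are required. Terms for randomisation block and a repeated-measures model over both follow-up visits are optional.

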### Health economic analysis

We will calculate the cost per participant for the CFT intervention, including training costs for group leads and travel costs for participants. We will also undertake some preliminary analyses to inform the economic evaluation that would accompany a full trial. This will be based on the premise that we will wish to estimate the incremental cost per QALY gained from the intervention versus control, and also the incremental cost per change in primary outcome. Consequently, we will collect data on the use of services (CSRI) and health-related quality of life (DEMQOL and EQ-5D-5L) and examine overall response rates and completion rates of individual questions.

### Patient and public involvement

Patients and the public have been involved since the project inception. The current proposal was developed in collaboration with our patient and public involvement (PPI) lead who attends most monthly management meetings and will be invited to coauthor publications and copresent to diverse audiences.

Our PPI advisory group consists of four people with various types of dementia, one of whom is from a South Asian community, and one family caregiver. They will meet at least four times including the manual adaptation, modifying the CSRI, devising the qualitative interviews and dissemination stages to ensure clarity for a lay audience. Our trial steering committee (TSC) also includes a family caregiver from a South Asian community, they will provide cultural insights to ensure the feasibility trial is relevant to South Asian communities.

